**Objective:**

**Primary objective:** To demonstrate superiority effect of incremental hemodialysis (HD) protocol (initiate with once-weekly HD) plus ketoanalogues-supplemented low-protein diet during non-dialysis days over the standard HD protocol (initiate with twice weekly HD) on preservation of residual renal function (renal urea clearance) at 12 months.

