**Methods:**

**Sample Size Calculation:**

As this is a pilot study, the sample size calculation will be based on recent suggestions for sample size estimation in pilot randomized trials by Whitehead et al. With 80% power and the alpha level = 5%, 20 patients per treatment arm are required based on the non-central t distribution (NCT) approach assuming a small standardized effect size ( $0.1 \leq \delta < 0.3$ ). With an anticipated the drop-out rate of 20%, 25 patients per treatment arm are adequate. Therefore, we aim to include a total of 50 patients in the study.

Target number of Patients: 50 incident hemodialysis patients will be randomized 1: 1 according to the frequency of dialysis per week, amount of protein prescribed, and receiving of ketoanalogues. Additionally, the different techniques of hemodialysis will be stratified by dialysis facilities as the followings (Fig 1):

- **Group 1:** Twice weekly HD program plus regular protein diet (1.0 g/kg/day) every day
- **Group 2:** Incremental HD program, starting from once weekly HD/HDF plus low protein diet (0.6 g/kg/day) and ketoanalogues supplementation on non-dialysis days and regular protein diet (1.0-1.2 g/kg/day) on dialysis day

[figure not shown]

(Figure S1)

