**Exclusion Criteria:**

- Rapid glomerular filtration rate (GFR) progression defined as a decline of eGFR  $>5$  ml/min/1.73m^2 by CKD-EPI equation in the prior 6 months before enrollment
- Presence of wasting diseases, cancer cachexia, tuberculosis, AIDS wasting syndrome
- Other active infection/inflammation determined by CRP  $>10$  mg/L
- Severe gastrointestinal problem: persistent nausea/vomiting, dysphagia, chronic diarrhea, severe malabsorption
- Conditions at baseline requiring withdrawal from the study including severe protein energy wasting by SGA and MIS score, prior kidney transplantation with immunosuppressive agents or other serious medical conditions.
- Pregnancy
- Uncontrolled hypercalcemia (persistent serum Ca  $\geq 10.5$  mg/dl)
- BMI  $\geq 35$  kg/m^2
- Hypersensitivity to the active substances or to any of the excipients of Ketosteril
- Disturbed amino acid metabolism

**Criteria for remaining on once-weekly HD for Group 2 (All patients must meet all criteria before randomization)**

- Residual kidney function  $\geq 3$  ml/min/1.73m^2 calculated by Chula urea kinetic model (UKM) formula
- Good dialysis adequacy defined by  $\text{eqKt/V} \geq 1.2$  /session and duration  $\geq 4$  hr/session
- Kru by Chula UKM formula  $< 3$  mL/min
- No signs of water retention (water retention defined as required ultrafiltration rate  $> 15$  ml/kg/hour for 3 consecutive visits)
- No history of active congestive heart failure, ischemic heart disease, acute coronary syndrome, and other pulmonary symptoms
- BMI  $< 35$  kg/m^2
- No persistent hyperkalemia (serum K  $> 5.5$  mEq/L) and hyperphosphatemia (serum phosphate  $> 5.5$  mg/dL) for more than 2 months
- No malnutrition (serum albumin  $< 3.5$  g/dL) and adhere to nutritional therapy
- Hemoglobin  $> 9$  g/dL and appropriate response to anemia therapy
- Infrequent hospitalization and easily manageable other comorbid conditions

**Criteria for remaining on twice-weekly HD for Group 1 and Group 2 (patients should meet first criteria plus  $\geq 5$  of other criteria)**

- Good dialysis adequacy: delivered standard Kt/V  $\geq 2.1$ /week
- No signs of water retention (defined as ultrafiltration rate  $> 15$  ml/kg/hour for 3 consecutive visits)
- No history of active congestive heart failure, ischemic heart disease, acute coronary syndrome, and other pulmonary symptoms

- Suitable larger body size relative to RKF

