- No persistent hyperkalemia (serum K >5.5 mEq/L) and hyperphosphatemia (serum phosphate >5.5 mg/dL) for > 1 months or 2 consecutive visits (2-week interval)
- No malnutrition (serum albumin <3.5 g/dL) and adhere to nutritional therapy
- Hemoglobin >8 g/dL and appropriate response to anemia therapy (erythropoietin dose adjustment is allowed for 1 visit)
- Infrequent hospitalization and easily manageable other comorbid conditions

After the protocol approval by IRB of Faculty of Medicine, Chulalongkorn University, the participants that willing to participate the study will sign in the informed consent. They will get into run-in period and then randomization.

After randomization, the attending nephrologists at each time point (3, 6, 9, and 12 months after randomization) will determine HD frequency by criteria. The HD frequency will be increase from once per week to twice per week in Group 1, if patients fail criteria for remaining on once per week HD. The HD frequency will be increase from twice per week to thrice per week in Group 2, if patients fail criteria for remaining on twice per week HD. Patients in Group 1 receiving twice per week HD will receive thrice per week HD if patients fail criteria for remaining on twice per week HD.

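### The step-up rule for dialysis frequency swaps the group labels, so the once-weekly arm has no written step from once to twice weekly

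*Protocol*

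**What the plan says.** Three places in the Protocol fix the starting frequency of each arm, and they agree.

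- **Primary objective.** The experimental strategy is the "incremental hemodialysis (HD) protocol (initiate with once-weekly HD"), to be shown superior "over the standard HD protocol (initiate with twice weekly HD").
- **Arm definitions (under Sample Size Calculation).** Group 1 is "Twice weekly HD program plus regular protein diet (1.0 g/kg/day) every day". Group 2 is "Incremental HD program, starting from once weekly HD/HDF plus low protein diet (0.6 g/kg/day") with ketoanalogues on non-dialysis days.
- **Headings of the criteria lists (within Exclusion Criteria).** One list is headed "Criteria for remaining on once-weekly HD for Group 2" and names no other group. The other is headed "Criteria for remaining on twice-weekly HD for Group 1 and Group 2".

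The step-up paragraph closes that same section, just before Study assessments/measurements. It has the attending nephrologists set the frequency by these criteria at 3, 6, 9 and 12 months after randomization. Three labelled sentences follow:

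1. "The HD frequency will be increase from once per week to twice per week in Group 1, if patients fail criteria" for staying on once-weekly treatment.
2. "The HD frequency will be increase from twice per week to thrice per week in Group 2", on failing the twice-weekly criteria.
3. Group 1 patients who are on twice-weekly treatment move to thrice weekly on failing the same criteria.

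**The concern.** The first sentence gives the once-to-twice step to the arm whose patients all start at twice weekly. Group 2 is the only arm that can be on once-weekly treatment after randomization, and it receives only the twice-to-thrice step. Read literally, a Group 2 patient who fails the once-weekly criteria has no labelled step to twice weekly.

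Dialysis frequency is part of the randomized strategy, so this paragraph helps to define the intervention being tested. The criteria lists give the conditions for staying at a frequency but name no action on failure; only this paragraph does. The once-weekly criteria include fluid retention, persistent hyperkalaemia, malnutrition and haemoglobin, so failing them matters clinically. The missing step is the first escalation for the patients who receive the least dialysis.

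There is also a smaller analytic point. The per-protocol population excludes anyone who departs from the assigned protocol. A Group 2 patient properly moved to twice weekly would be following a step that the paragraph does not state for that group, which leaves room for dispute over that patient's status.

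**Working it through.** The plan gives no figure to reproduce on this point. The check sets the steps that the design requires beside the steps that the paragraph states.

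**Required steps.** Group 1 starts at twice weekly and Group 2 at once weekly (primary objective and arm definitions). The once-weekly criteria cover Group 2 only, and the twice-weekly criteria cover both groups (list headings). A patient who fails the criteria for a frequency moves up one level. This gives:

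- Group 2, once to twice weekly;
- Group 1, twice to thrice weekly;
- Group 2, twice to thrice weekly.

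**Comparison with the step-up paragraph.**

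| Step | Required by the design | Stated as written | Stated after exchanging labels |
|---|---|---|---|
| Group 2, once to twice | yes | **no** | yes (sentence 1) |
| Group 1, twice to thrice | yes | yes (sentence 3) | yes (sentence 2) |
| Group 2, twice to thrice | yes | yes (sentence 2) | yes (sentence 3) |
| Group 1, once to twice | no; no such patient exists | **yes (sentence 1)** | no |

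**Count.** As written, 2 of the 3 required steps are stated, 3 − 2 = 1 is missing, and 1 stated step is void. After exchanging the labels, 3 of 3 are stated, none is missing and none is void.

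**Is it a swap or a single slip?** The third sentence is limited to patients who are on twice-weekly treatment at the time. That limit is redundant for Group 1, whose patients all start there. It makes sense for a group that began once weekly and may have stepped up, which is Group 2. All three sentences therefore read naturally once the labels are exchanged, which points to a consistent swap.

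**Could the run-in explain sentence 1?** No. The paragraph applies after randomization and depends on failing the once-weekly criteria, which are headed for Group 2. Whatever schedule Group 1 patients followed during the two-week run-in, they are on twice-weekly treatment from randomization.

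**The case against.** The strongest reply is that nobody would be misled. The objective, the arm definitions and both list headings agree on which arm starts where. The paragraph itself opens by telling nephrologists to set the frequency by the criteria, with no group label. On those terms, a Group 2 patient who fails the criteria for remaining on once-weekly treatment does not remain on it. Sentence 1 taken literally has no patient to act on, so a clinician would see the label is wrong. The missing step and the void step are one wrong label seen from two sides. Sentences 2 and 3 together already cover twice-to-thrice for both groups, so exchanging their labels changes nothing of substance. No analysis quantity moves, and classing a Group 2 step-up as a protocol deviation is unlikely when the twice-weekly list names Group 2.

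Much of this stands. The intent can be inferred, the substantive error lies in the first sentence, and the per-protocol worry is secondary. It is fairer to call this a labelling inconsistency than a poor design decision, because the design itself is settled. Figure S1 is not shown in the text reviewed and may set out the scheme, but the paragraph would still contradict the arm definitions.

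What does not follow is that the text can be left alone. It is the only statement of what to do when criteria are failed, and a nephrologist should not have to override the written rule to give a once-weekly patient more dialysis.

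**Conclusion.** The concern holds. The paragraph assigns the once-to-twice step to the wrong group: of three required step-ups it states two, omits the first escalation for Group 2, and includes one that applies to nobody. It should be fixed, because it governs part of the randomized intervention and a safety-relevant escalation.

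The limits are clear. The twice-to-thrice step is stated for both groups. Sample size, alpha and the primary intention-to-treat analysis, which compares patients as randomized, are unaffected. Only Group 2 patients who fail the once-weekly criteria reach the omitted step. The protocol gives no failure rate, so no number of affected patients is claimed, and nothing in the document shows that any patient would be managed differently.

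The conclusion rests on the arm definitions being correct and the step-up paragraph being the error. The objective, the definitions and the list headings all support that reading.

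**What to change.** Exchange Group 1 and Group 2 in all three sentences of the step-up paragraph, so that it reads in substance:

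- Group 2 patients move from once to twice weekly on failing the once-weekly criteria.
- Group 1 patients move from twice to thrice weekly on failing the twice-weekly criteria.
- Group 2 patients already on twice-weekly treatment move to thrice weekly on failing the same criteria.

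Correcting the label in the first sentence alone would also supply the missing step. Exchanging all three is better because the sentences then follow the order of escalation and the limit in the third sentence has a purpose. The cost is a wording correction to three sentences, with no extra patients, visits or procedures.

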### Study assessments/measurements

#### Clinical assessments

- Definition of death: death from all causes and/or death from renal failure
- Definition of hospitalization: All cause of hospitalization

**Laboratory assessments:** Blood samples were drawn after overnight fasting to determine blood parameters. Serum albumin was measured in duplicate using a nephelometer and the values averaged. Muscle mass was measured by multi-frequency BIS (InBody®).

**QoL assessments:** The subjects will be assessed QoL by SF-36 questionnaire Thai version.

#### Adverse events, serious adverse events,

Adverse events leading to premature discontinuation and all events resulting in death will be assessed throughout the study.

**Investigation period:** 12 months 2 weeks (run-in: 2 weeks + evaluation 12 months)

**Data collection:** 5 points (Baseline at randomization, 3, 6, 9, and 12 months after randomization)

#### Measurement:

[figure not shown]

Primary outcomes

[figure not shown]

Secondary outcomes

|  | Baseline | 3 months | 6 months | 9 months | 12 months |
|--|----------|----------|----------|----------|-----------|
|  |          |          |          |          |           |

|                                                                                                                      |   |       |   |       |   |
|----------------------------------------------------------------------------------------------------------------------|---|-------|---|-------|---|
| Urinary urea clearance by timed-urine volume (24 hours preceding dialysis treatment)                                 | X | X     | X | X     | X |
| Average of urinary urea and creatinine clearance (24 hours preceding dialysis treatment)                             | X | X     | X | X     | X |
| Nutritional parameters: weight, BMI, albumin, calcium, phosphate level, normalize protein catabolic rate (nPCR), SGA | X | X     | X | X     | X |
| Bioimpedance analysis                                                                                                | X | X     | X | X     | X |
| Other functional tests QoL (SF 36), B2microglobulin, P-cresol, indoxyl sulfate, anemia                               | X | ----- | X | ----- | X |

### Data Management Section

All data obtained in the clinical trial described in this protocol will be recorded on CRFs or trial specific entry forms. Data will be clearly documented in the Trial Documentation file which data will be collected as source data only. Laboratory data will be recorded electronically.

### Confidentiality of trial documents and patient records

The study will assure that subjects' anonymity will be maintained and that their identities are protected from unauthorized parties. On CRFs or other documents, subjects would not be identified by their names, but by an identification code. The investigator would keep a subject enrolment log showing codes, names and addresses. The investigator will maintain documents e.g., subjects' written consent forms, in strict confidence. Management of clinical data will be performed in accordance with applicable standards and data cleaning procedures to ensure the integrity of the data, e.g., removing errors and inconsistencies in the data.

### Safety Reporting

Adverse event reports are the critical building block to the development of the safety profile of the study. Subjects will be asked non-leading questions in general terms to determine the occurrence of AEs, according to the schedule outlined. In addition, all AEs reports spontaneously during the course of the study will be recorded. The investigator must immediately (within 24 hours of awareness) reports all SAEs, regardless of whether the investigator believes they are related to the study.

**Definition of an Adverse Event:** An AE can be any unfavorable and unintended sign (eg, an abnormal and clinically significant laboratory finding), symptom or disease temporally associated with the treatments without any judgment about causality. This includes any occurrence that is new in onset or aggravated in severity or frequency from the baseline condition, or abnormal results of diagnostic procedures, including laboratory test abnormalities.

An AE includes medical conditions, signs and symptoms not previously observed in the subject that emerge during the protocol-specified AE reporting period, including signs or symptoms associated with an underlying condition that were not present prior to the AE reporting period.

**Definition of a Serious Adverse Event:** All SAEs must be reported immediately. To report an SAE, the investigator must fax or email an SAE report within 24 hours of becoming aware of the serious event. Follow-up reports must be submitted in a timely manner as additional information becomes available. For each SAE observed, the investigator will obtain all of the information available about the event, including (but not limited to): hospital discharge diagnosis, hospital discharge note, death certificate, appropriate laboratory finding (including autopsies and biopsy results), and clinical examinations (including radiological examinations and clinical consultation).

An SAE is any AE or suspected adverse reaction that results in any of the following outcomes:

- Death
- A life-threatening AE (ie, if in the view of the investigator, the subject was at immediate risk of death at the time of the event).
- Inpatient hospitalization or prolongation of existing hospitalization
- A persistent or significant incapacity or substantial disruption of the ability to conduct normal life functions
- A congenital anomaly or birth defect
- An important medical event (based on appropriate medical judgment, the event jeopardizes the subject and may require medical or surgical intervention to prevent one of the above-listed outcomes)

#### **Reporting Serious Adverse Events to the Institutional Review Board/Independent Ethics**

**Committee:** The investigator is responsible of notifying Institutional Review Board (IRB), Faculty of Medicine, Chulalongkorn University of SAEs in accordance with the regulations.

#### **Analysis plan:**

For continuous variables, the descriptive statistics will be presented by number [N], mean and standard deviation [mean  $\pm$  SD] for normally distributed data, and minimum, median, interquartile ranges [Q1, Q3], and maximum for non-normally distributed data. For categorical variables, the number [N] and percentage [%] of each category will be calculated for non-missing data. Missing values will also be counted and reported in each variable for both continuous and categorical variables, if applicable. All analyses will be done per treatment and per time-point."

Treatment estimates and 95% confidence intervals will be calculated and used to assess primary and secondary efficacy endpoints between randomized treatment groups.

Continuous endpoints will be analyzed using ANCOVA or non-parametric equivalents. Longitudinal analyses for continuous endpoints will be conducted using general linear mixed model (GLM). Post-hoc pairwise comparisons will be conducted using Tukey's HSD. Binary endpoints will be analyzed using chi-square tests or logistic regression. The statistical test will be two-sided with significance level  $\alpha = 5\%$ . Due to the exploratory nature of the pilot study, P values will be interpreted as a merely descriptive-exploratory purpose."

For all endpoints and analysis populations, the primary treatment comparisons will be simple, unadjusted, two group comparisons. If there are important imbalances in baseline characteristics, then adjusted analyses will also be performed and presented in addition to unadjusted analyses.

Data on demographics, protocol and treatment compliance, concomitant medication and safety of all included subjects (including dropouts) will be included in the trial report. Demographics, safety data at randomization and concomitant medication will be listed. Descriptive statistics will be calculated for the subject characteristics. There will be no formal comparisons of randomized treatments for demographic and baseline characteristics (i.e. no p-values), as any imbalance will by definition have occurred by chance.

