### **Primary study endpoint analysis**

The primary endpoint is the reduction of renal urea clearance after 12 months of treatment compared between the two treatment groups.

The ITT population will be the primary analysis dataset, although an analysis on the PP population will also be performed.

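### The Analysis plan states the primary analysis of renal urea clearance two incompatible ways, ANCOVA and unadjusted; the unadjusted rule is valid but less precise

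*Protocol*

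**What the plan says.** All of this is in the protocol.

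- **Analysis plan, methods by endpoint type:** "Continuous endpoints will be analyzed using ANCOVA or non-parametric equivalents". No covariate is named. Longitudinal analyses of continuous endpoints are assigned to a mixed model.
- **Analysis plan, next paragraph:** "For all endpoints and analysis populations, the primary treatment comparisons will be simple, unadjusted, two group comparisons".
- **Analysis plan, directly after that:** "If there are important imbalances in baseline characteristics, then adjusted analyses will also be performed and presented in addition to unadjusted analyses". No threshold and no list of characteristics is given, and the section rules out baseline significance tests.
- **Primary study endpoint analysis:** "The primary endpoint is the reduction of renal urea clearance after 12 months of treatment compared between the two treatment groups". It makes the ITT population primary but names no statistical method.
- **Data collection:** visits are "Baseline at randomization, 3, 6, 9, and 12 months after randomization". The Measurement table lists urinary urea clearance at each of them, so a baseline value is planned for every patient.
- **Sample Size Calculation, paragraph on the target number of patients:** "Additionally, the different techniques of hemodialysis will be stratified by dialysis facilities as the followings".

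The Analysis plan also says that endpoints are assessed by treatment estimates with 95% confidence intervals, and that P values are only exploratory.

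**The concern.** Two analysts could each follow this protocol and report different primary estimates and intervals, one from ANCOVA and one from a plain two-arm comparison. This is not detail left for a later analysis plan: the protocol itself fixes the primary comparison, and does so twice.

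The choice has consequences. In a trial of 50 patients judged on estimates and intervals, interval width is the main thing the analysis can still influence. Baseline renal urea clearance is measured and is the natural predictor of the month-12 value. An unadjusted comparison does not use it efficiently, and an arm that happens to start with higher or lower clearance carries part of that difference into the result. Under the second rule, adjustment appears only if an imbalance is judged important, a judgement with no stated criterion that is made once the data are in view.

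**Working it through.** **1. The two sentences side by side.** Renal urea clearance is continuous, so the ANCOVA sentence covers it. The other sentence covers all endpoints, so it covers it too. One calls for a covariate and the other excludes adjustment. The primary-endpoint section gives no method, so nothing in the protocol gives one sentence precedence.

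**2. The plan's own figures.** The protocol gives no correlation, standard deviation or precision target for clearance, so there is no stated precision figure to reproduce. The dropout step does reproduce: 20/0.8 = 25 per arm, 50 in total. I use 20 per arm below, the protocol's number before the dropout allowance. Nothing here depends on how that 20 was obtained.

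**3. Precision.** Assumptions: the same standard deviation at baseline and month 12, and a baseline-to-month-12 correlation rho of 0.3 to 0.9. In units of that variance, the per-patient variances are:

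- month-12 value alone: 1
- change from baseline: 2(1 − rho)
- ANCOVA on baseline: 1 − rho²
- ANCOVA relative to change: (1 − rho²)/[2(1 − rho)] = (1 + rho)/2

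| rho | Change | ANCOVA | ANCOVA/change | SE lower by | Unadjusted n per arm to match ANCOVA with 20 | ANCOVA/month-12 value |
|---|---|---|---|---|---|---|
| 0.3 | 1.40 | 0.91 | 0.65 | 19% | 20/0.65 = 30.8 | 0.91 |
| 0.5 | 1.00 | 0.75 | 0.75 | 13% | 20/0.75 = 26.7 | 0.75 |
| 0.7 | 0.60 | 0.51 | 0.85 | 8% | 20/0.85 = 23.5 | 0.51 |
| 0.8 | 0.40 | 0.36 | 0.90 | 5% | 20/0.90 = 22.2 | 0.36 |
| 0.9 | 0.20 | 0.19 | 0.95 | 2.5% | 20/0.95 = 21.1 | 0.19 |

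The change-score columns fit the endpoint as the primary-endpoint section defines it. The last column applies only if the month-12 value alone is compared, a possible reading of the Primary objective.

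**4. Cost of estimating the slope.** With n per arm, fitting the baseline slope inflates the ANCOVA variance on average by 1 + 1/(2n − 4). For n = 20 this is 1 + 1/36 = 1.028. The net ratio is 0.65 × 1.028 = 0.67 at rho 0.3 and 0.95 × 1.028 = 0.98 at rho 0.9. The gain is real over most of the range and nearly gone at the top of it.

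**5. Chance imbalance.** The difference in mean baseline between arms of 20 has a standard deviation of √(2/20) = 0.32 baseline SDs. A one-standard-deviation imbalance moves the change-score contrast by (1 − rho) × 0.32: 0.22 SD at rho 0.3, 0.16 at 0.5, 0.09 at 0.7 and 0.03 at 0.9. The sample-size section has in mind a standardized effect of 0.1 to just under 0.3. This is the loss in step 3 seen in a single trial, not an additional one: at rho 0.3, 1.40 − 0.91 = 0.49 = 0.7².

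**6. If facility is a randomization stratum.** Simulated unadjusted t-tests (two equal strata, 20 per arm balanced within strata, 40,000 runs) reject a true null at the nominal 5% level in 5.1%, 4.5%, 3.9%, 2.8% and 2.0% of trials when strata explain 0, 5, 10, 20 and 30% of the outcome variance. These shares are assumed. Ignoring a true stratum makes the test conservative.

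**The case against.** The best defence is that the two sentences do different jobs. ANCOVA with the outcome's own baseline would be the general method, and unadjusted would mean only that no other patient characteristics enter. This is strained, because baseline clearance is itself a baseline characteristic and the next sentence makes adjustment for such characteristics conditional. Even on this reading the text needs one clarifying line.

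It is also fair to say that an unadjusted randomized comparison is unbiased over randomization, that the trial is a pilot with exploratory P values, and that the gain depends on a correlation the protocol does not give. All of that stands. It limits the consequence to precision and clarity.

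Three stronger readings may tempt a reader, and the protocol does not support them:

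- **That baseline clearance is discarded.** The primary endpoint is a reduction over 12 months. A change score uses each patient's baseline with a fixed coefficient of 1, so the loss is partial. It would be discarded only if month-12 values alone were compared.
- **That randomization is stratified by facility.** The text says "the different techniques of hemodialysis will be stratified by dialysis facilities". It stands in the randomization paragraph, but it could mean that technique varies by site. Facility is not expressly named as a randomization stratum, and the accompanying figure is not shown.
- **That the imbalance trigger lets the more favourable result become the primary one.** Adjusted analyses come on top of the unadjusted ones and do not replace them. What remains is an undefined trigger and room for emphasis between two reported results, not type I error inflation.

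**Conclusion.** The point holds as a contradiction about the primary analysis, together with an avoidable loss of precision if the unadjusted sentence governs. Assuming equal standard deviations and a correlation of 0.3 to 0.9, ANCOVA variance is 0.65 to 0.95 of the unadjusted change-score variance. At 20 per arm that is equivalent to about 11 extra patients per arm at the low end of the correlation range and about 1 at the high end. The contradiction itself needs no assumption; it is in the text.

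The unadjusted comparison is valid but less efficient. No bias over randomization and no excess of false positives has been shown, and none should be claimed. The protocol should be changed, but the point does not threaten the trial's validity.

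**What to change.** Replace the sentence that makes every primary comparison unadjusted, at least for the primary endpoint, with one statement along these lines: the primary comparison of renal urea clearance at 12 months is an ANCOVA (or the month-12 contrast of the mixed model) with baseline renal urea clearance as a prespecified covariate.

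- Clarify in the sample-size and allocation paragraph whether randomization is stratified by facility or technique. Only if it is, add that factor to the model, with sparse sites pooled.
- Report the unadjusted comparison as supportive.
- Do not make adjustment of the primary endpoint depend on observed imbalance.

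The cost is wording, since baseline clearance is already scheduled. The baseline covariate uses one residual degree of freedom (38 to 37 with 20 per arm), and a stratification factor would use a few more, depending on the number of sites, which the protocol does not state.
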